# Improvement of synaptic plasticity and cognitive function in RASopathies—a monocentre, randomized, double-blind, parallel-group, placebo-controlled, cross-over clinical trial (SynCoRAS)

**DOI:** 10.1186/s13063-023-07392-z

**Published:** 2023-06-06

**Keywords:** RASopathies, Neurofibromatosis type 1, Noonan syndrome, Transcranial magnetic stimulation, Synaptic plasticity, Attention, Lovastatin, Lamotrigine

## Abstract

**Background:**

Cognitive impairment is a common medical issue in rat sarcoma (RAS) pathway disorders, so-called RASopathies, like Neurofibromatosis type 1 (NF1) or Noonan syndrome (NS). It is presumed to be caused by impaired synaptic plasticity. In animal studies, pathway-specific pharmacological interventions with lovastatin (LOV) and lamotrigine (LTG) have been shown to improve synaptic plasticity as well as cognitive function. The aim of this clinical trial is to translate the findings of animal studies to humans and to probe the effect of lovastatin (NS) and lamotrigine (NS and NF1) on synaptic plasticity and cognitive function/alertness in RASopathies.

**Methods:**

Within this phase IIa, monocentre, randomized, double-blind, parallel-group, placebo-controlled, cross-over clinical trial (syn. SynCoRAS), three approaches (approaches I–III) will be carried out. In patients with NS, the effect of LTG (approach I) and of LOV (approach II) is investigated on synaptic plasticity and alertness. LTG is tested in patients with NF1 (approach III). Trial participants receive a single dose of 300 mg LTG or placebo (I and III) and 200 mg LOV or placebo (II) daily for 4 days with a cross-over after at least 7 days. Synaptic plasticity is investigated using a repetitive high-frequency transcranial magnetic stimulation (TMS) protocol called quadri-pulse theta burst stimulation (qTBS). Attention is examined by using the test of attentional performance (TAP). Twenty-eight patients are randomized in groups NS and NF1 with *n* = 24 intended to reach the primary endpoint (change in synaptic plasticity). Secondary endpoints are attention (TAP) and differences in short interval cortical inhibition (SICI) between placebo and trial medication (LTG and LOV).

**Discussion:**

The study is targeting impairments in synaptic plasticity and cognitive impairment, one of the main health problems of patients with RASopathies. Recent first results with LOV in patients with NF1 have shown an improvement in synaptic plasticity and cognition. Within this clinical trial, it is investigated if these findings can be transferred to patients with NS. LTG is most likely a more effective and promising substance improving synaptic plasticity and, consecutively, cognitive function. It is expected that both substances are improving synaptic plasticity as well as alertness. Changes in alertness may be a precondition for improvement of cognition.

**Trial registration:**

The clinical trial is registered in ClinicalTrials.gov (NCT03504501; https://www.clinicaltrials.gov; date of registration: 04/11/2018) and in EudraCT (number 2016–005022-10).

**Supplementary Information:**

The online version contains supplementary material available at 10.1186/s13063-023-07392-z.

## Background

Disorders of the rat sarcoma (RAS) pathway, so-called RASopathies, such as Noonan syndrome (NS), neurofibromatosis type 1 (NF1), Costello syndrome (CS), LEOPARD syndrome and the cardio-facio-cutaneous syndrome (CFC), share common clinical and cognitive deficits that range from poor motor coordination, learning and attention deficits to severe mental retardation [1]. Cognitive impairment is a common medical issue in these patients and variable in its expression. It is presumed to be caused—at least in part—by impaired synaptic plasticity due to dysregulated RAS signalling in neurons [1].

The pathophysiology of cognitive deficits in RASopathies has been studied using a mouse model of NF1. Mice heterozygous for a null mutation of the NF1 gene (Nf1 + / −) have spatial learning problems. It has been shown that hyperactivation of the RAS pathway in these mice leads to an impairment of synaptic plasticity, and pharmacological or genetic approaches that reverse the enhancement in RAS-MAPK (rat sarcoma–mitogen-activated protein kinases) signalling in Nf1 + / − mice also reverse their synaptic plasticity and spatial learning deficits [2, 3]. It is assumed but has not been shown, so far, that the activating mutations in agonists of the RAS-MAPK signalling pathway leading to NS, CFC and CS basically have similar impacts on neuronal function and synaptic plasticity as the loss-of-function in an agonist such as in NF1. In animal studies, pathway-specific pharmacological interventions with lovastatin (LOV) have been shown to improve synaptic plasticity as well as cognitive function [4, 5].

In humans, deficits in synaptic plasticity have been shown in patients with NF1 [6] as well as in patients with NS [7] which were associated with attention deficits [6], reviewed in [8]. In patients with NF1, we have demonstrated in a placebo-controlled, short-term intervention that RAS pathway modulation by LOV reduces gamma-aminobutyric acid (GABA)ergic inhibition and improves synaptic plasticity as well as attention [6, 8]. Hence, we were able to translate the results from animal studies to humans with NF1. This principle of a pathway-specific pharmacological intervention restoring impaired synaptic plasticity and improving cognitive function has been demonstrated in placebo (PLC) controlled intervention with LOV for 4 days [6].

The study of Mainberger et al. [6] also revealed the mechanism of impaired synaptic plasticity in humans with NF1 (*n* = 11) which was associated with increased GABAergic inhibition. The mechanism that GABA is regulating synaptic plasticity has been described previously as “gatekeeping mechanism” [9]. Decreasing intracortical inhibition by LOV was associated with an increase in synaptic plasticity in patients with NF1 [6]. The central role of intracortical inhibition regulating synaptic plasticity in NF1 has recently been certified by animal studies revealing a new option of pharmacological intervention with Lamotrigine (LTG) [5]. The authors have previously demonstrated that LTG is a potent modulator of synaptic plasticity in healthy humans [10].

It is expected and we hypothesize that both substances (LTG and LOV) improve synaptic plasticity as well as alertness in patients with NS and NF1. Changes in alertness may be a precondition for improvement of cognition. The results may contribute to the treatment of patients on an individual level as well as a basis for the initiation of larger multicentre clinical trials.

## Methods

### Aim of the study

The aim of this study is to investigate changes in synaptic plasticity and alertness in patients with RASopathies, namely NS and NF1, after the application of lovastatin (to NS patients) and lamotrigine (to NS and NF1 patients).

### Design

The SynCoRAS study is a monocentre, randomized, double-blind, parallel-group, placebo-controlled, cross-over clinical trial phase IIa. The trial design is shown in Figs. 1 and 2. The clinical trial has been approved before trial commencement by the local ethics committee (vote 461/17 Af dated 13–02-2018, with the last amendment No. 3 dated 12–11-2020) and by the German medical regulatory authorities (Federal Institute for Drugs and Medical Devices (Bundesinstitut für Arzneimittel und Medizinprodukte (BfArM)). Prior start of recruitment the clinical trial was registered in ClinicalTrials.gov (https://www.clinicaltrials.gov) as well as in the European Union (EU) Clinical Trials Register (EudraCT-Nr.: 2016–005022-10).

**Fig. 1 Fig1:**
[figure not shown]
Graphical flowchart of the study design for NS (experiment I and II). In experiment I, patients with Noonan syndrome first receive lamotrigine (LTG) or placebo (PLC) with a minimum pause of 7 days and maximum of 60 days. In experiment II, lovastatin (LOV) or PLC with a minimum pause of 7 days and maximum 60 days. Between experiments, there will be a pause of at least 14 days

**Fig. 2 Fig2:**
[figure not shown]
Graphical flow-chart of the study design for NF1 (experiment III). In experiment III, patients with NF1 first receive lamotrigine (LTG) or placebo (PLC) with a minimum pause of 7 days and maximum of 60 days

### Study population

Inclusion criteria are defined as follows: (1) Group 1: NS, Group 2: NF1 (both genetically assured); (2) age ≥ 16 years; (3) signed informed consent of the adolescent (16–17 years of age) who is capable to give his consent and understand the aim and rationale of the study and of the legal guardian; (4) signed informed consent of persons who are ≥ 18 years old and capable to give their consent. In case of doubts, an independent medical practitioner will evaluate the capacity to consent; (5) male and female participants who are not capable of bearing children or who use a method of contraception that is medically approved by the health authority of the respective country.

Exclusion criteria are (1) epilepsy, (2) participants taking medication with known central nervous system (CNS) effects, (3) severe mental retardation, (4) side effects during previous medication with and contraindications for LTG and/or LOV and/or transcranial magnetic stimulation (TMS), (5) psychiatric diseases, (6) previous history of allergic reactions with LTG and LOV medications, (7) potentially unreliable patients, (8) patients who are not suitable for the study in the opinion of the investigator, (9) pregnancy (incl. positive urine pregnancy test) and (10) persons who are incapable of giving consent or do not understand the aim or rationale of the study.

### Interventions

Participants are randomized into either one out of the three approaches (exp. I–III). Three randomizations take place—one for each experiment. Patients are randomly assigned to receive either first verum then placebo, or vice versa. The randomization lists were created using RANCODE professional 2015. Randomization is performed block-wise. The randomization list was provided to the pharmacy for blinding, labelling and distribution of trial medication. For the case of emergency unblinding, a second set of sealed envelopes includes the information on the type of medication for each randomization number and is stored at the trial site. The integrity of the envelopes is monitored until end of study.

#### Experiment I—Lamotrigine (LTG) in patients with NS

Participants receive 300 mg single dose LTG or placebo 2 h before TMS, corresponding to the peak plasma time of LTG [11]. After at least 7 (up to 60) days, a cross-over takes place: participants receive placebo or 300 mg single dose LTG 2 h before TMS (Fig. 1).

#### Experiment II—Lovastatin (LOV) in patients with NS

Participants receive 200 mg LOV or placebo daily for 4 days prior to TMS. On the day of TMS, the medication is given 3 h before starting TMS corresponding to the peak plasma concentration of LOV [12]. After at least 14 (up to 60) days, a cross-over takes place: participants receive placebo or 200 mg LOV daily for 4 days prior to TMS (Table 1, Additional file 1). On the day of TMS, the medication is given 3 h before starting TMS.

**Table 1 Tab1:** Schedule of procedures and visits patient group 1, NS

*Study overview medication*	**Base-line (or day 1)**	**Visit 1 (day 1)** **D1**	**Visit 2 (min. 7—60 D after V 1)** **D8–61**	**Visit 3 (min. 14–60 D after V2)** **D22–121**	**Visit 4 (3 D after V3)** **D25–124**	**Visit 5 (min. 14–60 D after V4)** **D39–184**	**Visit 6 (3 D after V5)** **D42–187**
		**Exp. I: Lamotrigine (LTG) vs. placebo, single dose (with cross-over)**		**Exp II: Lovastatin (LOV) vs. placebo 4 days (with cross-over)**			
Informed consent	**X**						
Eligibility criteria	**X**						
Demographics	**X**						
Medical/surgical history	**X**						
Vital signs	**X**	**X**	**X**	**X**		**X**	
Pregnancy test^a^	**X**			**X**			
Randomization		**X**		**X**			
Exp. I: LOV or PLC) Four days				**X**	**X**	**X** **(cross-over)**	**X**
Exp. II: LTG or PLC) Single dose		**X**	**X** **(cross-over)**				
TMS (electromyography (EMG) integrated)^b^		**X**	**X**		**X**		**X**
TAP		**X**	**X**		**X**		**X**
Concomitant medication	**X**	**X**	**X**	**X**	**X**	**X**	**X**
AE/SAE		**X**	**X**	**X**	**X**	**X**	**X**

^a^To be performed after having obtained informed consent; if baseline is less than 5 days prior to V1, a second pregnancy test is not necessary

^b^TMS to be performed 3 h after intake of LOV and 2 h after intake of LTG

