#### Experiment III—Lamotrigine (LTG) in patients with NF1

Participants receive 300 mg single dose LTG or placebo 2 h before TMS [11]. After at least 7 (up to 60) days, a cross-over takes place: participants receive placebo or 300 mg single dose LTG 2 h before TMS (Table 2, Additional file 1).

**Table 2 Tab2:** Schedule of procedures and visits patient group 2, NF1

*Study overview medication*	**Baseline visit (or day 1)**	**Visit 1 (day1)** **D1**	**Visit 2 (7–60 days after V 1)** **D8–61**
		Exp. III: Lamotrigin (LTG) or Placebo	
Informed consent	**X**		
Eligibility criteria	**X**		
Demographics	**X**		
Medical/surgical history	**X**		
Vital signs	**X**	**X**	
Pregnancy test^a^	**X**	**X**	
Randomization		**X**	
Exp. III: LTG or PLC) Single dose		**X**	**X** **(cross-over)**
TMS (EMG integrated)^a^		**X**	**X**
TAP		**X**	**X**
Concomitant medication	**X**	**X**	**X**
AE/SAE		**X**	**X**

^a^To be performed after having obtained informed consent; if baseline is less than 5 days prior to V1, a second pregnancy test is not necessary

^b^TMS to be performed 2 h after intake of LTG

Experiments I and II take place with a sufficient time gap on the same set of patients (Fig. 1). It is not possible to conceal treatment in a triple cross-over design in group 1, which is why two separate tests have been planned on group 1.

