**Experiment III**			
Local α	0.050	0.025	0.017
Power with 14 patients	94%	97%	99%
Power with 12 patients	90%	94%	97%

An increase in MEP amplitudes over time is considered to refer to the concept of long-term potentiation (LTP)-like plasticity as it has been demonstrated in Mainberger et al. [7] as well. Twelve patients per disease entity will be enough to provide appropriate power to all planned primary endpoint tests (two-sided paired samples *t*-tests) with a global significance level of 5% and adjusted local significance levels using the Bonferroni-Holm procedure. In order to account for some unobtainable data and drop outs, the sample size will be increased to 14 patients per disease (28 trial participants in total).

Analysis sets: For each experiment, there will be a separate analysis set defined, as it is possible that a patient is suitable for analysis in only one of the first two experiments. All analyses will be performed on the full analysis set (FAS-I, FAS-II, FAS-III), consisting of all patients who delivered a full set of MEP measurements within the corresponding experiment. Since all measurements will take place within a very short time per patient, it is expected that the data will be either complete or entirely missing.

Primary endpoint: The primary endpoint analyses will be performed in three separate testing procedures. The global significance level will be 5%. Since experiments I and II are done on the same set of patients, the significance level for those two experiments will each be 2.5%. The significance level of experiment III will be 5%. The primary endpoint analysis will consist of three series of three paired samples two-sided* t*-tests, comparing MEP under verum vs. placebo at the three measurement time points. The local significance level will be adjusted using the Bonferroni-Holm procedure and will be as follows for the ordered by *p*-value tests:

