### Trial status

The current protocol version number is “Final 5.0 AM 3.0”, date 9/21/2020. Recruitment finished on 3/30/2023 prematurely due to unforeseen difficulties in recruitment of patients. Recruitment was still open on initial submission of the manuscript. Recruitment began in March 2018, and an actual number of 16 participants have been enrolled. A large panel including the sponsor-delegated person, the head of German Network of RASopathy Research (GeNeRARe) and the Sponsors representative for risk-based quality management decided to prematurely close the recruiting and to terminate the study in retrospect on 2/20/2023 due to the last patient last visit (LPLV) taking place on 2/9/2023.

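### Table 1 (Noonan syndrome) marks pregnancy tests at Baseline and V3 only, but its footnote waives a repeat test that only makes sense at V1

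*Protocol article*

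**What the plan says.** Table 1 of the protocol article (schedule for group 1, NS) marks the pregnancy test at Baseline and at Visit 3. The cells for V1, V2, V4, V5 and V6 are empty. Footnote a on that row requires consent before the test and then adds: "if baseline is less than 5 days prior to V1, a second pregnancy test is not necessary".

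Table 2 (schedule for group 2, NF1) has the same footnote, word for word, but marks the test at Baseline and V1.

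The treatment at V1 is the same in both groups. Experiment I (NS): "Participants receive 300 mg single dose LTG or placebo 2 h before TMS, corresponding to the peak plasma time of LTG". Experiment III (NF1): "Participants receive 300 mg single dose LTG or placebo 2 h before TMS".

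Under Study population, exclusion criterion 9 is "pregnancy (incl. positive urine pregnancy test)". Inclusion criterion 5 admits "male and female participants who are not capable of bearing children or who use a method of contraception that is medically approved".

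**The concern.** The footnote sets its condition on the interval from baseline to V1. Such a condition can sensibly switch off only a repeat test at V1. In Table 2 that test is marked and the rule works. In Table 1 the rule has no V1 test to act on, and the only later test marked is at V3, before the lovastatin experiment.

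A site using Table 1 has to guess which test is meant. Going by the marks, it would give lamotrigine or placebo at V1 without a repeat, however old the baseline test was. Taking the footnote to mean the only second test in the row, it would drop the V3 test because of an interval that says nothing about pregnancy status weeks later. In either case a check on a stated exclusion criterion is lost before a dose.

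**Working it through.** No power or alpha formula applies. The check is a cell-by-cell comparison of the two tables, plus the visit arithmetic.

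**1. The rows side by side**

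| Schedule | Baseline | V1 | V2 | V3 | V4 | V5 | V6 |
|---|---|---|---|---|---|---|---|
| Table 1, NS | X | – | – | X | – | – | – |
| Table 2, NF1 | X | X | – | not applicable | not applicable | not applicable | not applicable |

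The Table 1 row has all seven visit cells. Its V3 mark lines up with the V3 mark in the Randomization row just below, which also shows a V1 mark in the right column. A column shift in the extracted text is therefore unlikely.

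**2. Reproducing the article's visit window (Table 1 header)**

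- V1 = D1.
- V2 is 7 to 60 days after V1: D1 + 7 = D8 to D1 + 60 = D61.
- V3 is 14 to 60 days after V2: D8 + 14 = D22 to D61 + 60 = D121.

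This matches the printed D22–121. V3 thus falls 22 − 1 = 21 to 121 − 1 = 120 days after V1.

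**3. Main reading: the footnote concerns a repeat at V1**

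Let g be the number of days from baseline to V1. The waiver applies if g < 5, that is 0 to 4 whole days; a repeat is implied if g ≥ 5.

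- g = 0 to 4: no V1 test either way, so nothing changes.
- g ≥ 5, Table 1 as marked: test age at the V1 dose = g, at least 5 days.
- g ≥ 5, with a V1 repeat as in Table 2: test age = 0 days.

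**4. Literal alternative: the second test is the one marked at V3**

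The waiver applies with g = 0 to 4. Test age at the first lovastatin or placebo dose (V3) would be:

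- minimum: 22 − 1 + 0 = 21 days;
- maximum: 121 − 1 + 4 = 124 days;
- with the V3 test kept: 0 days.

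A gap of under 5 days before V1 gives no reason to skip a test at least 21 days later, so this reading is the less plausible one.

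**5. How many participants**

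The ceiling is the planned NS group. Under Analyses and statistics, "the sample size will be increased to 14 patients per disease (28 trial participants in total)", so at most 14. The article does not give the number who can bear children or the number with a baseline 5 or more days before V1, so the true figure cannot be derived.

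**The case against.** The strongest reply is that the footnote already carries the instruction. Saying a repeat is unnecessary when baseline is recent implies that it is necessary otherwise, so on the main reading only a redundant mark is missing, and untested dosing occurs only if a site reads the grid and ignores the note. This is right as to what the authors probably meant. It does not remove the conflict: the marks omit the V1 test, and the note, applied to the row as printed, points at V3.

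Several other points also carry weight:

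- Both schedules allow lamotrigine dosing at V2, 7 to 60 days after V1, with no test marked there. In Table 1 the second lovastatin or placebo course starts at V5, which is 3 + 14 = 17 to 3 + 60 = 63 days after V3. A test a little over 5 days old is not extreme beside these intervals. That limits the importance of the point but does not make the row and footnote agree.
- Table 2 is not a perfect template. For the same lamotrigine regimen it marks vital signs at V1 only, where Table 1 marks V1 and V2, and its TMS row carries the wrong footnote letter. Table 1 also swaps the Experiment I and II labels on its drug rows. These look like copying slips in the article, and the full German protocol may be correct.
- Little can be acted on now. The Trial status section says the study was terminated in retrospect "due to the last patient last visit (LPLV) taking place on 2/9/2023", and 16 participants in total were enrolled across both diseases.

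These points keep the matter minor. They do not show that Table 1 is right as printed, and the complaint is not about detail left to the full protocol: the article prints both the schedule and the rule, and the two conflict.

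**Conclusion.** The concern holds as a minor error in a safety schedule. The pregnancy-test row of Table 1 and its footnote do not fit together, and the most plausible explanation is a missing conditional mark at V1, with the V3 test meant to stand.

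The consequence on that reading is a test at least 5 days old, rather than 0 days, at the V1 dose for NS participants whose baseline was 5 or more days earlier. The 21 to 124 days applies only under the less plausible literal reading and should not be taken as the expected effect.

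The mismatch itself is certain from the printed tables. That the mark belongs at V1 is an inference from the footnote's condition and from Table 2. Inclusion criterion 5 limits the risk on either reading. Nothing in the article shows that a test was in fact missed. The statistical analysis is not touched.

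**What to change.** In Table 1, add a conditional mark at V1 in the pregnancy-test row and keep the mark at V3. Reword footnote a along these lines: *the V1 test may be omitted when baseline took place fewer than 5 days before V1; the V3 test is always required.* Footnote a of Table 2 can stay as it is.

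The cost is one table mark and one sentence. In practice it would have meant one urine test at V1 for NS participants with a baseline 5 or more days old, which the footnote already implies. With the last visit completed, no future dose is affected; the change corrects the published schedule, and the full protocol should be checked for the same wording.
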